##### Sample size calculation

###### General practitioner study

Sample size calculation refers to the primary endpoint and is based on a t-test (α = 0.05; power = 0.8). We assume that HbA1c in the intervention group will decrease on average by 0.2%-points (standard deviation (sd) of 2.3) compared to the control group. The estimator results from the assumption that at least 50% of T2DM-patients have a need for periodontitis therapy [15, 20] and that they’re able to lower their HbA1c by 0.6%-points through therapy [8]. Out of these patients, an assumed 66% will use the referral to a dentist [21]. To account for cluster effects (patients clustered in practices), an intra-class-correlation of 0.03 and a cluster size of 10 patients per practice is assumed. For the control group calculated from claims data, we assume that it contains at least double the number of patients than the intervention group (allocation in a 2:1 ratio for control vs. intervention group). This results in a sample size of 1980 intervention patients (198 practices, 10 patients each) and 3960 control patients. With an assumed drop-out rate of 20%, there will be 2480 intervention patients (248 practices, 10 patients each) and 4950 control patients. Sample size calculation was performed using PASS v16.0.3.

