### Statistical hypotheses and analyses

#### General practitioner study

For the primary outcome, we will test the null hypothesis H_0_^HA^: µ_IG_^T1−T0^ = µ_KG_^T1−T0^ against the alternative hypothesis H_1_^HA^: µ_IG_^T1−T0^ ≠ µ_KG_^T1−T0^ on a two-sided significance-level of 5%. µ_IG_^T1−T0^ and µ_KG_^T1−T0^ represent the reduction of the HbA1c-parameter between baseline (T0) and after 4 quarters (T1) in both groups.

Evaluation of the intervention contains descriptive and explorative statistical analyses of gathered study data as well as available claims data. The goal is an independent, scientifically valid and differentiated statement on effectiveness of the intervention regarding a reduction of the HbA1c parameter using an intervention study with parallel control group. The control group will be calculated from insurer claims data as well as DMP-documentation data across insurers. Using their registration number, intervention practices will be removed from the control group data. Study data will be described using descriptive methods.

Primary analysis will be a hierarchical, linear mixed model representing the multi-level structure of the data (level 1: practice, level 2: patient). For the test of H_0_^HA^, the dependent variable will be “reduction of HbA1c between T0 and T1”. The model contains the practice as a random effect and HbA1c at baseline (T0), age, sex, insurance status, state and residential area as fixed effects on the patient level. Here, only variables that are also included in claims data can be used.

It can be assumed that claims data will be complete and missing values will only occur in the additional study data and the questionnaires. Missing values of the primary outcome will be imputed using multiple imputation [27] while accounting for the baseline-variables age, sex, insurance status and residential area. Assumptions on missing values will be analyzed and an alternative procedure to handle missing data, such as an analysis of the full dataset, will be looked into.

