#### Dentist study

For the primary outcome, we will test the null hypothesis H_0_^ZA^: π_IG_^T1−T0^ = π_KG_^T1−T0^ against the alternative hypothesis H_1_^ZA^: π_IG_^T1−T0^ ≠ π_KG_^T1−T0^ on a two-sided significance-level of 5%. π_IG_^T1−T0^ and π_KG_^T1−T0^ represent the rate of new diabetes diagnoses between baseline (T0) and after 12 months (T1) in both groups.

Primary analysis will be performed using a generalized, logistic mixed model adequately representing the multi-level structure of data (practice on level 1, patients on level 2). For the test of H_0_^ZA,^ the „rate of new diabetes diagnoses between T0 and T1” will be used as the dependent variable. The model contains the practice as a random effect and the group (intervention vs. control), age, sex, insurance status, state and residential area as fixed effects on the patient level.

It can be assumed that claims data will be complete and missing values will only occur in the additional study data and the questionnaires. Missing values of the primary outcome will be imputed using multiple imputation [27] while accounting for the baseline-variables age, sex, insurance status and residential area. To check for the sensitivity of results, assumptions on missing values will be analyzed and an alternative procedure to handle missing data, such as an analysis of the full dataset, will be looked into. Further sensitivity analyses include sub-group analyses for both states and for insurance status.

Secondary endpoints will be presented descriptively first. Where appropriate, secondary endpoints will be explored similar to the primary analysis. For binary endpoints, logistic regression analyses will be performed. For continuous endpoints, linear regression analyses will be performed. For all estimated effects we will present descriptive p-values and 95% confidence intervals. All analyses are performed using a validated R environment with R version 4.0.0 or higher. The primary analysis is independently counter-programmed in SAS version 9.4 or higher.

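### The printed imputation list for both primary outcomes is narrower than the analysis models; if it is run on both groups pooled, leaving out group shrinks the treatment effect

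*Protocol article*

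**What the plan says.** Protocol article, Statistical hypotheses and analyses, General practitioner study. The primary model is described as follows: "The model contains the practice as a random effect and HbA1c at baseline (T0), age, sex, insurance status, state and residential area as fixed effects". Two paragraphs later, missing primary outcomes are to be "imputed using multiple imputation [27] while accounting for the baseline-variables age, sex, insurance status and residential area". On where values can be missing: "It can be assumed that claims data will be complete and missing values will only occur in the additional study data and the questionnaires".

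Protocol article, Statistical hypotheses and analyses, Dentist study. The primary model, in which every term after practice is a fixed effect: "The model contains the practice as a random effect and the group (intervention vs. control), age, sex, insurance status, state and residential area as fixed". The imputation sentence is the same: "Missing values of the primary outcome will be imputed using multiple imputation [27] while accounting for the baseline-variables age, sex, insurance status and residential area".

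Both null hypotheses compare intervention with control. Nowhere does the article say that imputation is run by group, uses group as a predictor, or is multilevel. An additional analysis of the full dataset is promised under Analytic population as a sensitivity analysis. In the two study sections it appears as an alternative still to be considered.

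**The concern.** Multiple imputation is valid for a given analysis when the imputation model holds at least the terms of that analysis. Here the article names the imputation variables, and the list is shorter than its own analysis models.

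The omissions do different things:

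- **Group.** If missing outcomes are drawn from one distribution fitted to both groups, imputed patients show no treatment difference, and the estimate is pulled toward zero even when loss is completely random.
- **Practice.** Imputed values carry no between-practice variation. This mainly misstates the clustering and the standard error.
- **State, and baseline HbA1c in the GP study.** Leaving these out biases the result only if missingness depends on them, and the bias can go either way.

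At stake is the size of both primary estimates, and the 80% power that the sample sizes were built to deliver at a drop-out rate the plan itself expects.

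**Working it through.** **Inputs** (Protocol article, Sample size calculation).
- GP study: effect 0.2 %-points, SD 2.3, ICC 0.03, 10 patients per practice, control:intervention 2:1, drop-out 20%, 2480 intervention and 4950 control patients.
- Dentist study: rates 0.10 and 0.05, ICC 0.03, 8 patients per practice, drop-out 20%, 664 per group.
- Both: α = 0.05 (two-sided in the hypotheses), power 80%.
- Assumed for this check: the missing fraction equals the drop-out rate, and values are missing completely at random.

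**The plan's own sample sizes reproduce.** With (1.960 + 0.842)² = 7.849:
- GP: 7.849 × 2.3² × (1 + 1/2) / 0.2² = 1557.0, rounded up to 1558. Times 1 + 9 × 0.03 = 1.27 gives 1979, so 198 practices of 10 = 1980. 1980/0.8 = 2475, rounded up to 2480. Controls 3960/0.8 = 4950.
- Dentist: 7.849 × (0.10 × 0.90 + 0.05 × 0.95) / 0.05² = 431.7. Times 1 + 7 × 0.03 = 1.21 gives 522.3, so 66 practices of 8 = 528. 528/0.8 = 660, rounded up to 664.

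**Dentist study, imputation pooled without group, 20% missing in each arm.** The pooled mean is 0.075.
- Intervention: 0.8 × 0.10 + 0.2 × 0.075 = 0.095.
- Control: 0.8 × 0.05 + 0.2 × 0.075 = 0.055.
- Risk difference 0.040 instead of 0.050 (−20%). Marginal odds ratio 1.80 instead of 2.11.
- Power with group in the imputation: effective n = 664 × 0.8/1.21 = 439; SE = √(0.1375/439) = 0.0177; Φ(0.050/0.0177 − 1.96) = 81%.
- Power without group: Φ(0.040/0.0177 − 1.96) = 62%. With the smaller SE that treats imputed values as observed (n = 664/1.21 = 549; SE = √(0.13795/549) = 0.0159) it is 71%.

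**GP study, one model fitted to both groups, missing values in the intervention arm only.** Observed: 2480 × 0.8 = 1984 intervention and 4950 control patients, so 4950/6934 = 71% of the fitting data are controls.
- Effect: 0.8 × 0.2 + 0.2 × (0.2 × 1984/6934) = 0.171 instead of 0.20 (−14%).
- SE = 2.3 × √(1/1984 + 1/4950) × √1.27 = 0.0689. Power falls from Φ(0.2/0.0689 − 1.96) = 83% to Φ(0.171/0.0689 − 1.96) = 70%.
- If the imputation is fitted within the intervention arm, no control value enters and the effect stays at 0.20.

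**Range by missing fraction**

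| Missing | Dentist RD | Dentist power, with group → without | GP effect (pooled) | GP power, with group → without |
|---|---|---|---|---|
| 10% | 0.045 | 85% → 77-81% | 0.186 | 86% → 80% |
| 20% | 0.040 | 81% → 62-71% | 0.171 | 83% → 70% |
| 30% | 0.035 | 75% → 46-60% | 0.156 | 79% → 58% |

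**Simulation check** (clustered data, ICC 0.03, 20% missing, 10 imputations, Rubin's rules, analysis of cluster means; GP controls taken as 495 practices of 10).
- Dentist, 2000 replicates: with group 0.049 and 82% power; without group 0.0395 and 70%.
- GP, 1500 replicates: with group 0.203 and 85%; without group 0.173 and 78%.
- A separate simulation with cluster-robust variance gave 83% → 73% for the dentist study (1500 replicates). Its GP run (600 replicates) gave 88% → 76%. The 88% lies several Monte Carlo standard errors (√(0.88 × 0.12/600) = 0.013 each) above the formula's 83%, so it is not used.
- GP under the null: 2.5% rejections without group, 4.9% with group. The lower figure arises because the Rubin standard error (0.066) exceeds the empirical SD of the estimate (0.058).

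**The case against.** The strongest reply is that the exclusion of group is inferred. The sentence names baseline variables to be accounted for and does not say that only these are used. Group is not a baseline covariate, and the article's lists are visibly incomplete: the printed GP analysis model also lacks group, although its hypothesis cannot be tested without it. A condensed article may leave the full imputation specification to a SAP that is not shown. This stands in part, and it is why the attenuation is put conditionally. It does not explain the other gaps. State and baseline HbA1c are baseline variables, they are in the analysis models, and they are missing from a list that names its members.

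A second reply is that GP claims data are taken to be complete, so missing outcomes lie in the intervention group and a model fitted to the study data alone gives no attenuation. This stands fully. The text does not say which data the model is fitted to.

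A third reply is that the additional full-dataset analysis protects the result. If it means complete cases, it would show no attenuation under random loss. It is only a sensitivity analysis, however, so the attenuated estimate would remain primary.

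A reader might also infer that every omitted term pulls the effects toward zero, or that leaving out baseline HbA1c loses the strongest predictor of change. The first is wrong, since only omitting group does this. For the second, the documents give no figure.

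**Conclusion.** The point holds in a limited form. As printed, the imputation list is narrower than the analysis model in both studies, and this is something the article states rather than leaves open.

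The harm that can be sized comes from group. If imputation is run as listed on both groups pooled, with 20% missing completely at random, then:
- in the dentist study the risk difference falls from 0.050 to 0.040 and power from about 81% to roughly 62-73%;
- in the GP study the effect falls from 0.20 to about 0.17 and power from about 83% to about 70-78%, solely if intervention and control patients share one imputation model.

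The spread in power reflects the standard error used. At 10% missing the loss is small, and GP power by formula is still about 80%.

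The documents do not support the stronger reading that both primary estimates are certain to be biased, because they do not state that group is excluded or that the arms are pooled. Nor is there a false-positive risk: under the null, a shared distribution is the correct one, and the GP simulation was conservative. The danger is an understated or missed effect.

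**What to change.** In both study sections under Statistical hypotheses and analyses, state that the imputation model contains every term of the analysis model: group (or imputation run separately by group), state, practice through a multilevel imputation method and, in the GP study, baseline HbA1c, in addition to the four variables already named. For the GP study, also say whether the model is fitted to intervention patients alone or together with the controls. Using T2 values as auxiliary variables is optional.

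The cost is one sentence per study and slightly more complex imputation code. No further patients or data are needed. If imputation by group is already intended, the same sentence removes the ambiguity.

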#### Dentist study

For the primary outcome, we will test the null hypothesis H_0_^ZA^: π_IG_^T1−T0^ = π_KG_^T1−T0^ against the alternative hypothesis H_1_^ZA^: π_IG_^T1−T0^ ≠ π_KG_^T1−T0^ on a two-sided significance-level of 5%. π_IG_^T1−T0^ and π_KG_^T1−T0^ represent the rate of new diabetes diagnoses between baseline (T0) and after 12 months (T1) in both groups.

Primary analysis will be performed using a generalized, logistic mixed model adequately representing the multi-level structure of data (practice on level 1, patients on level 2). For the test of H_0_^ZA,^ the „rate of new diabetes diagnoses between T0 and T1” will be used as the dependent variable. The model contains the practice as a random effect and the group (intervention vs. control), age, sex, insurance status, state and residential area as fixed effects on the patient level.

It can be assumed that claims data will be complete and missing values will only occur in the additional study data and the questionnaires. Missing values of the primary outcome will be imputed using multiple imputation [27] while accounting for the baseline-variables age, sex, insurance status and residential area. To check for the sensitivity of results, assumptions on missing values will be analyzed and an alternative procedure to handle missing data, such as an analysis of the full dataset, will be looked into. Further sensitivity analyses include sub-group analyses for both states and for insurance status.

Secondary endpoints will be presented descriptively first. Where appropriate, secondary endpoints will be explored similar to the primary analysis. For binary endpoints, logistic regression analyses will be performed. For continuous endpoints, linear regression analyses will be performed. For all estimated effects we will present descriptive p-values and 95% confidence intervals. All analyses are performed using a validated R environment with R version 4.0.0 or higher. The primary analysis is independently counter-programmed in SAS version 9.4 or higher.

#### Process evaluation

Quantitative data will primarily be analyzed descriptively for the GP and the dentist study. Categorial variables will be presented in absolute and relative frequencies. Continuous variables will be presented using mean values with standard deviation or median values using interquartile range, minimum and maximum. Differences between groups will be analyzed using variance analyses. Changes between T0 and T1 will be exploratively tested for influences on implementation adherence using regression analyses. Analyses will be performed using IBM SPSS statistics.

The transcribed, semi-structured phone interviews will be analyzed in inductive and deductive phases. In the deductive phase, interview data will be analyzed using a thematic framework analysis to classify and organize data on the base of key topics, concepts and pre-defined categories. Analysis will be performed using MAXQDA.

Qualitative and quantitative data will be integrated using a framework analysis [28, 29]. Topics emerging from the data will be assigned to the identified areas of the framework (e.g. CFIR [24] or TICD [25]). Results from both parts of the process evaluation will then be combined using an integrative analysis [30].

#### Economic evaluation

A cost-cost-analysis will compare total costs for periodontitis- and diabetes-specific treatments in the intervention group with a representative control group. Simultaneously, a corresponding benefit-benefit-analysis will, in the context of a difference-in-differences analysis, analyze subjective health changes of study participants over the course of the study between intervention and control group.

In case of a positive or inconclusive result of these first analyses on the advantages of the intervention, the incremental cost-effectiveness-relation (ICER) of the intervention will be calculated in comparison to usual care and based on DMP and claims data as well as results from the main and process evaluation. Furthermore, there will be calculations on costs and effects of the transfer of the intervention to usual care. To calculate the ICER, differences in the costs will be compared with differences in health effects. Costs of usual care will be calculated from claims data [10]. Additional costs caused by the intervention will be estimated on the base of documented costs from the study and approximated personnel costs from the results of the process evaluation (time spent for the intervention multiplied with usual rates for personnel costs). All analyses will be performed using a validated R-environment with R version 4.2.2. or higher.

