## Evaluation approach

### Impact evaluation

#### Study in general practices and dental practices

The GP study is a practice-based, multi-center, non-randomized, controlled trial. The intervention group will be recruited in general practices, the control group will be calculated from insurer claims data as well as from DMP documentation data across insurers (triangulation in comparison to the insurer-data) parallel to the clinical intervention group.

The dentist study is a practice-based, multi-center, cluster-randomized, controlled trial with a control and an intervention group. Both groups are recruited in dental practices. Patients are clustered in practices, hence a randomization on cluster-level was deemed appropriate.

Both studies will be carried out in the German states of Baden-Württemberg and North Rhine-Westphalia.

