###### Dentist study

Dental practices are assigned to a control and intervention group in a 1:1 ratio using a central, web-based tool (randomizer.at) to avoid any manipulation and ensure concealed allocation. Randomization will be stratified by state and use a block-wise randomization process with a varying length of blocks to arrive at groups of equal size and avoid selection bias. Randomization will take place on the practice (cluster) level, so all participants within a given practice will either be part of the intervention or the control group. The randomizing tool will be administered by the evaluating Institute of Medical Biometry at the Heidelberg University Hospital.

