##### Baseline survey (T0)

Patients in both studies receive a written questionnaire on sociodemographic data and a self-disclosure of medical conditions. The questionnaire further contains a question on current, subjective health, translated from the publicly available, validated Short Form 36 (SF-36)-questionnaire by RAND Corporation [23]. Additionally, the questionnaire contains the respective questions for periodontitis/T2DM risk assessment (in the dentist study, this is only the case for the intervention group), so patients may calculate their risk score. The medical/dental assistant will be available for questions during this process. The further course differs depending on the study and risk-score.

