##### Survey T1 (first follow-up)

The medical assistant in the general practice identifies all participating patients during a regular DMP-appointment. In the dental practice, the dental assistant identifies all participating patients during a regular appointment. Patients are asked to fill out another written questionnaire on their health and a potential periodontitis/T2DM diagnosis and therapy. Subjective health is once again assessed using the first question of the SF-36. To allow for a comparison with the patient’s subjective health at T0, question 2 of the SF-36 will be asked as well.

In the GP-study, the GP asks the patients about their potential periodontitis diagnosis and/or therapy. The primary endpoint measured during the regular DMP-appointment as well as the questionnaire data (including secondary endpoints) for T1 will be transferred to the research database by the medical assistant.

In the dentist study, the dentist in both control and intervention group asks the patients about their potential T2DM diagnosis and/or therapy. The current periodontal status and the periodontal services provided will, together with the questionnaire data, be transferred to the research database by the dental assistant.

The second, and final, follow-up survey takes place 6 to 12 months after T1, depending on when the patient was recruited for T0.

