##### Survey T2 (second follow-up)

The medical/dental assistants identify patients similar to T1. Patients in general practices are asked to fill out another written questionnaire on their health and a potential periodontitis diagnosis and therapy as well as the first two questions of the SF-36. These data and the current HbA1c-parameter will be transferred to the research database. T2 serves the purpose of checking on a permanent reduction of the HbA1c-parameter and to get a long-term picture of the secondary endpoints as well.

Patients in the dental practice are asked to fill out another written questionnaire on their health and a potential T2DM diagnosis and therapy as well as the first two questions of the SF-36. These data and the current periodontal status and the periodontal services provided will be transferred to the research database. T2 here serves the purpose of getting a long-term picture of the secondary endpoints.

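### Difference-in-differences for subjective health gives up precision that adjusting for the T0 answer would keep in the randomised dental study

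*Protocol article*

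**What the plan says.** Under Statistical analyses, Economic evaluation, the protocol article pairs a cost comparison with a benefit comparison. The method of the benefit comparison is given as follows: "in the context of a difference-in-differences analysis, analyze subjective health changes of study participants over the course of the study". It sets the intervention group against the control group. The section does not say which of the two studies is meant, and it gives no time points or covariates.

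The design sections narrow this down:

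- **Dental study, design.** "The dentist study is a practice-based, multi-center, cluster-randomized, controlled trial with a control and an intervention group" (Study in general practices and dental practices). "Dental practices are assigned to a control and intervention group in a 1:1 ratio" (Randomization procedure, Dentist study).
- **Dental study, data.** At T0, for both studies, "The questionnaire further contains a question on current, subjective health"; only the risk-assessment questions are confined to the dental intervention group. At T1, "Subjective health is once again assessed using the first question of the SF-36". At T2, dental patients report on "a potential T2DM diagnosis and therapy as well as the first two questions of the SF-36".
- **GP study.** "The control group will be calculated from insurer claims data as well as DMP-documentation data across insurers" (Statistical hypotheses and analyses, General practitioner study). Quality of life in GP practices is listed as coming from primary data only, and the additional survey data are described for intervention patients.

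On what follows from the benefit result, the Economic evaluation section says: "In case of a positive or inconclusive result of these first analyses on the advantages of the intervention", the ICER will be calculated, comparing cost differences with differences in health effects.

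**The concern.** Difference-in-differences compares change scores, which fixes the coefficient of the baseline answer at 1. It is usually chosen for groups that were not randomised, where a stable difference between them has to be removed and parallel trends can be argued. In a randomised comparison that removal is not needed for validity. Estimating the baseline coefficient instead of fixing it at 1 gives a smaller residual variance.

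The dental study is the only one shown where the planned contrast can be formed from patients' own answers in both groups, and the T0 answer needed for adjustment is already collected. The article also adjusts for a baseline value elsewhere: the GP primary model includes HbA1c at T0, although its outcome is already a change. The Economic evaluation section gives no reason for the less precise choice. At stake is the width of the interval around the subjective-health difference.

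**Working it through.** **1. The plan's own figure for the randomised comparison.** No sample size is stated for the benefit analysis, so the dental sample size is the reference. Inputs, from Sample size calculation, Dentist study: rates 0.10 and 0.05, unpooled Z-test, two-sided 5%, power 80%, ICC 0.03, 8 patients per practice, 20% drop-out.

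- Per group, unclustered: (0.10 × 0.90 + 0.05 × 0.95) × (1.960 + 0.842)² / 0.05² = 431.7
- Design effect: 1 + (8 − 1) × 0.03 = 1.21; 431.7 × 1.21 = 522.3, or 65.3 practices, rounded up to 66 × 8 = 528
- Drop-out: 66 / 0.8 = 82.5, rounded up to 83 × 8 = 664

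Both stated figures, 528 and 664, are reproduced.

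**2. Variance of the two estimators.** Let s0 and s1 be the standard deviations at T0 and follow-up, and r their correlation.

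- Change score: s0² + s1² − 2·r·s0·s1
- Baseline-adjusted: s1²(1 − r²)
- Difference: (s0 − r·s1)², which is never negative

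With s0 = s1 = 1 these become 2(1 − r) and 1 − r². Their ratio is 2(1 − r)/(1 − r²) = 2/(1 + r), which exceeds 1 for every r below 1.

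**3. Numbers.** The article does not give r, so a range is shown. The last two columns use 528 analysed patients per arm and apply the design effect of 1.21 to both estimators. That takes over the ICC of 0.03, which the article assumes for new diagnoses and not for subjective health. SE = √(2 × variance × 1.21 / 528), in SD units. The equivalent n is 528 × (1 + r)/2.

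| r (assumed) | Variance ratio 2/(1 + r) | Interval-width ratio | SE, change score / adjusted | Equivalent n per arm |
|---|---|---|---|---|
| 0.4 | 1.43 | 1.20 | 0.074 / 0.062 | 370 |
| 0.5 | 1.33 | 1.15 | 0.068 / 0.059 | 396 |
| 0.6 | 1.25 | 1.12 | 0.061 / 0.054 | 422 |
| 0.7 | 1.18 | 1.08 | 0.052 / 0.048 | 449 |

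Below r = 0.5 the change-score variance 2(1 − r) exceeds 1, so it is also less precise than comparing follow-up answers alone.

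**4. Check under clustering.** A simulation with 66 practices of 8 per arm, ICC 0.03, no true effect and 3,000 runs per setting compared the difference in mean change with a regression on group and T0 answer. Practice-level correlation between T0 and follow-up was varied. Variance ratios were 1.33 to 1.50 at r = 0.4, 1.27 to 1.41 at 0.5, 1.21 to 1.34 at 0.6 and 1.16 to 1.24 at 0.7. The mean estimate was within 0.003 SD of zero for both methods in every setting, so neither is biased.

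**5. What the interval width decides.** The Economic evaluation section sends both a positive and an inconclusive first-stage result to the same next step, the ICER. The first stage also includes the cost comparison. A wider benefit interval that turns a positive reading into an inconclusive one therefore leaves the decision to calculate the ICER unchanged.

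**The case against.** **Patient selection after allocation.** This is the strongest argument for the stated method. Practices are randomised, not patients. The insurer authorisation form applies to intervention groups only and must be returned before a practice is included; practice staff recruit patients after that (Recruitment). Allocation therefore appears to be known when patients are approached, and baseline differences could be selective. If selection produced a stable difference D at T0 and follow-up, difference-in-differences would remove it, while adjustment with slope r would leave (1 − r)·D, half of it at r = 0.5. This stands as a small downside of the change and a reason to report both estimates. The article does not offer it as a reason, and it does not displace baseline adjustment as the standard choice for a randomised comparison.

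**A regression is already planned.** Quality of life is a dental secondary endpoint, to be explored where appropriate along the lines of the primary model, which has practice, group and state. That is most of the proposed model. The T0 answer is not among the listed covariates, however, and the economic section names a different method.

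**The text is condensed.** One clause in an article does not give the full model, and the full protocol may refine it. That is fair for covariates and time points. The method itself is named here, though, and the point concerns only that choice.

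**Stronger readings that the article does not support.** A reader might infer that difference-in-differences is biased here; under randomisation it is not. A reader might infer that lost precision could block the ICER, but an inconclusive result still leads to it. A reader might also take this estimate as the ICER's health effect. The section bases the ICER on DMP and claims data and on results of the main and process evaluation, and does not name this estimate.

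**Conclusion.** The point holds as a cheap improvement. For the dental study the stated change-score comparison has 2/(1 + r) times the variance of a baseline-adjusted one: 1.43 to 1.18 for r from 0.4 to 0.7, or intervals about 20% to 8% wider. The direction needs only a randomised comparison with a measured baseline. The size rests on equal T0 and follow-up variances and on r, which the article does not state. It also rests on reading the dental study as the place where the comparison is made, since no other study is shown with the item in both groups. The consequence is a less precise benefit estimate in a non-confirmatory economic analysis. Validity, the primary endpoints and the sample sizes are not affected.

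**What to change.** Change one sentence in Statistical analyses, Economic evaluation, so that it says:

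- for the dental study, the main estimate of the subjective-health effect is the group difference from a linear mixed model of the answer at T1 (and T2) on group, T0 answer and state, with practice as a random effect;
- difference-in-differences is kept as a sensitivity analysis, and both estimates are reported. A marked disagreement between them should prompt a look at whether recruitment was selective.

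No new data are needed, because the T0 answer is already collected in both dental arms. The cost is the one sentence and one additional model.
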